## Abstract

**Introduction:**

Childhood traumatization can result in physical and mental health problems in adulthood, such as post-traumatic stress disorder (PTSD), which negatively influences quality of life and social functioning. Although evidence based trauma treatments benefit clients with PTSD after childhood abuse and comorbid personality disorders, they are less effective than in clients who were traumatized in adulthood, and drop-out is substantial. The current study aims to assess the effects of inpatient dialectical behavior therapy combined with prolonged exposure (DBT-PTSD) on severity of PTSD, dissociation, parasuicidal behavior and borderline personality disorder (BPD) in clients with severe PTSD and comorbid psychiatric disorders. Secondary outcomes are social functioning, quality of life, borderline and cluster C personality disorder symptoms as treatment predictors, treatment trajectories, clients’ experiences and health economic consequences.

**Methods:**

The naturalistic, longitudinal Trauma Therapy Study is conducted from January 2019 until May 2025 in a mental healthcare center in the Netherlands. Clients with severe PTSD and comorbid conditions who are referred to inpatient DBT-PTSD are included into the study. Based on power analyses a total sample size of N=56 is needed. Measurements take place before the waiting list period, at pre- and posttreatment and at six- and twelve-months follow-up. Clients fill in a daily DBT-PTSD diary, which gives insight into individual symptom trajectories.

**Results:**

Statistical analyses include two-sided paired samples t-tests, linear mixed model analyses and cost-effectiveness analyses. Qualitative interviews are conducted within two years posttreatment and analyzed using a phenomenological approach. We correct for chance capitalization by using a conservative α-level of.01. Multiple imputation is used to handle missing data.

**Discussion:**

Research on the effects of integrated treatment programs for clients with severe PTSD and co-morbid conditions is scarce. This study extends current knowledge on the effects of inpatient DBT-PTSD on PTSD and BPD symptoms, clients’ social functioning and quality of life. In addition, it provides insight into individual symptom trajectories and experiences, inspiring future treatment improvements for clients with severe psychopathology.

**Trial registration:**

Medical Ethical Committee approval (NL669060018, RTPO1044/01.10.2018). Preregistration: Dutch registration database Centrale Commissie Mensgebonden Onderzoek and International Clinical Trials Registry Platform (NL-OMON46167/01.10.2018/https://trialsearch.who.int/Trial2.aspx?TrialID=NL-OMON46167).

## Introduction

1

Adverse childhood experiences, like physical, sexual or emotional abuse can lead to physical and mental health problems in adulthood (1), including post-traumatic stress disorder (PTSD) or complex PTSD (see **Box 1**). PTSD symptoms, like intrusions, avoidance, negative trauma-related cognitions and mood and hyperarousal (4) have a great negative impact on quality of life (5) and social functioning (6, 7). PTSD has a life-time prevalence of 3.9% (8) and often co-occurs with mental health problems, such as depression, anxiety, dissociation, substance use disorders, eating disorders and borderline personality disorder (BPD) (9–13). Clients with histories of severe childhood trauma seem to experience more severe PTSD symptoms and dissociation (14, 15), have more trouble with emotion regulation (14) and report a poor quality of life (5). Also, a greater number of childhood trauma types is related to a poorer mental and physical quality of life (16).

Box 1The International Classification of Diseases 11th Revision (ICD-11) differentiates between PTSD, complex PTSD and borderline personality disorder. Complex PTSD includes negative self-concept, relational problems and emotion regulation difficulties (2). Although the classifications complex PTSD and borderline personality disorder seem to overlap, most studies conclude that they are distinct classifications (3). The Diagnostic and Statistical Manual of Mental Disorders, Fifth Edition Text Revision (DSM-5-TR) classifies PTSD as a single condition (4). Since the mental healthcare system of the Netherlands uses the DSM-5-TR, in this study we define PTSD and BPD accordingly.

Although clients with PTSD after childhood abuse do benefit from evidence-based treatments (17, 18), there is room for improvement. For one, pooled drop-out rates vary between 16% and 41.5% (19, 20), appear to be greater in trauma-focused therapies and with childhood abuse-related PTSD (19, 21). Further, symptoms seem to improve to a lesser extent after interpersonal trauma (22), for clients with complex PTSD after childhood (sexual) abuse (23) and for clients with comorbid personality disorders (24). Also, emotion regulation and quality of life do not automatically improve after PTSD treatment, as shown in a systematic review and meta-analysis (18). For example, women with PTSD after childhood trauma reported very modest quality of life improvements that moved from ‘very low’ before Cognitive Processing Therapy to ‘low’ afterwards (5). Recently, more integrated and personalized interventions were suggested to improve treatment results (25, 26).

One such approach is the integration of Dialectical Behaviour Therapy (DBT) and Prolonged Exposure (PE). Several groups have studied a combination of PE and DBT, to make PTSD treatment accessible for clients with complex psychopathology, including high-risk behavior (27), and to address the needs of clients with chronic PTSD after childhood sexual abuse (28, 29). A systematic review and meta-analysis of inpatient and outpatient treatments that combine DBT and PE finds that PTSD and depressive symptoms decrease (30). Steil et al. (2011) developed inpatient DBT-PTSD for clients with severe PTSD after childhood sexual abuse. This treatment program of 12 weeks is based on DBT principles, includes PE as primary trauma-focused intervention and incorporates elements of Acceptance and Commitment Therapy and Compassion Focused Therapy (31). In a pilot (N=29) and RCT (N=74), with a Treatment As Usual (TAU) waiting list condition, women with and without comorbid BPD reported significant and clinically relevant improvements in PTSD after inpatient DBT-PTSD (28, 29). Drop-out was low in both RCT groups (DBT-PTSD: N=2, 5.5%; Control: N=3, 7.9%). Finally, in an observational study clients reported more improvement in PTSD symptoms, dissociation and disturbances in self-organization after inpatient DBT-PTSD than those treated with an inpatient TAU that included group interventions and trauma-focused treatment (32).

So far, these results of integrating DBT and PE are promising for clients with severe PTSD, comorbid BPD and a history of childhood sexual abuse. At the same time, studies on inpatient DBT-PTSD are still rather scarce. Replication of the results in various clinical settings and with a greater variation in PTSD client populations, regarding gender and a wider variety of trauma histories, are needed to inform treatment guidelines and clinical practice. Furthermore, little is known about predictors of treatment. In general, clients with PTSD and comorbid personality disorders seem to benefit somewhat less from PTSD treatments (24), but exploratory analyses showed that comorbid BPD was not predictive of DBT-PTSD treatment outcome (29). To improve our knowledge about client characteristics that may predict treatment outcome in DBT-PTSD, it is important that other personality disorders are also taken into account. In addition, obtaining a better insight into client perspectives and experiences with DBT-PTSD may also help improve this treatment. Finally, we are interested in the economic impact of DBT-PTSD, because the economic consequences of childhood trauma in terms of productivity loss and health care cost are high and increase with greater severity and complexity of the associated psychopathology (33–35).

The primary aim of this longitudinal, within-subjects study is to assess the effect of inpatient DBT-PTSD on PTSD severity in clients with severe PTSD and comorbid disorders. Secondary outcomes are dissociation, parasuicidal behavior, comorbid BPD symptoms, social functioning and quality of life. We hypothesize that PTSD, dissociation, parasuicidal behavior and BPD symptoms will decrease significantly after DBT-PTSD, in contrast to no significant changes after the waiting list period. Since DBT-PTSD offers training and therapy beyond trauma-focused treatment, we hypothesize improvements in quality of life and social as well. Especially at the six and twelve months follow-up measurements, as clients were able to pick up their daily lives after leaving the clinic. A more exploratory aim is to study whether BPD and cluster C personality disorder symptoms predict the effects of DBT-PTSD on PTSD symptoms. The fourth objective is to study the cost-effectiveness of inpatient DBT-PTSD. Finally, we intend to study clients’ experiences with the treatment program and, more exploratory, the individual differences in symptom trajectories.

## Methods

2

### Study design

2.1

The Trauma Therapy Study (TTS) is a naturalistic, longitudinal study with a within-subjects design. It takes place at GGZ Friesland, a mental health institute in The Netherlands from January 2019 to May 2025. Clients referred to inpatient DBT-PTSD are assessed at the beginning of the waiting list period (T0), at pre (T1) and posttreatment (T2) and at six (T3) and twelve months (T4) follow-up (**Figure 1**). The waiting list period is estimated to be approximately 12 weeks, based on the year before the start of the study. It may vary in length depending on the number of referrals to inpatient DBT-PTSD and unforeseen circumstances. When the waiting list period exceeds the three months, the baseline measurements are repeated to create a three months period between baseline and start of the intervention. Pre to posttreatment differences are compared to the control period, the pre to post waiting list period. During this period clients could continue any form of TAU to treat PTSD, as this is the case in everyday clinical practice.

**Figure 1 f1:**
[figure not shown]
Flowchart of the Trauma Therapy Study procedure.

### Procedure

2.2

Clients eligible for DBT-PTSD are first informed about the study during the commitment interview. The importance of truly committing to the treatment is then discussed and afterwards clients committed to DBT-PTSD are then placed on the waiting list. Those interested in study participation are sent detailed written information and receive a follow-up telephone call to provide further information. Clients are informed that study participation entails extra questionnaires and interviews, beside the standard diagnostic procedures and Routine Outcome Measurements (ROM).

During the baseline assessment (T0), informed consent is obtained by the research nurse. Interviews are performed by independent research assistants and clinical psychologists (in training). The interviewers are trained in the use of the instruments and regularly attend group intervision meetings to enhance reliability. Clients complete self-report questionnaires online. To improve study participation and retention clients can choose between being interviewed at the mental healthcare facility of via video call, This is particularly convenient for those living far away from the treatment center. We also approach clients enrolled in the TTS who finished DBT-PTSD in the previous two years and invite them for a qualitative interview about their experiences. These interviews are conducted by two clinical psychologists in training (AK and PV) who are unacquainted with these clients. Clients give an additional informed consent before starting this interview. Finally, we use the DBT-PTSD diary data from clients that started DBT-PTSD between 2019 (when the diary was digitalized) and December 2023 to study symptom trajectories. Clients fill in this daily diary as part of the treatment program.

### Ethical statement

2.3

The Medical Ethical Committee (METc) granted ethical approval for the second version of this protocol (nr. NL669060018, RTPO1044, date: 1 October 2018) and the subsequent amendment of 2 September 2022, to include a qualitative study. The study is preregistered at the Dutch registration database Centrale Commissie Mensgebonden Onderzoek and the International Clinical Trials Registry Platform (NL-OMON46167) and at the Center for Open Science (osf.io/74be8, https://doi.org/10.17605/OSF.IO/W3BHZ).

Clients are informed that they can stop study participation at any moment. Adverse events are recorded and serious adverse events are reported to the sponsor and the MEtc. The sponsor will suspend the study if there is sufficient ground that continuation of the study will jeopardize participants’ health or safety. Anonymized ROM assessments of non-participants is used to test for selection bias, except when clients opted-out and wanted their data removed from the research database of the mental health institute. This applies to the anonymized use of diary data of both participants and non-participants as well. As a standard procedure at GGZ Friesland, a colleague of the research department who is not involved in the project oversees the progress of the study. We followed the SPIRIT writing guidelines (36) and added the SPIRIT checklist to the submission of this study protocol.

### Participants

2.4

Clients aged 18–65 are eligible for inpatient DBT-PTSD if they meet the DSM-5 diagnostic criteria for PTSD and suffer from severe psychopathology. This includes various comorbid disorders. Trauma type is not leading in the indication process, but clients referred to the treatment center have often suffered from severe interpersonal traumas during childhood. Exclusion criteria employed by the treatment center are (1) current psychosis; (2) substance dependence; (3) a body-mass-index < 17 (because of the sports modules); (4) antisocial personality disorder; (5) war veterans; (6) clients with a recent severe suicide attempt in the last two months. Clients capable of comprehending the assessments are eligible to participate in the study.

### DBT-PTSD

2.5

This inpatient, modular DBT-PTSD treatment program of 12 weeks largely follows the original protocol developed by Bohus and colleagues (28, 29). **Table 1** provides an overview of all treatment modalities. Protocol modifications include the addition of four exposure sessions (total 16) and systemic therapy. In general, the treatment consists of three phases and has both fixed and optional modules. In phase 1 (weeks 1 - 2) clients identify values they find important in life and goals they wish to work on during and after finishing the treatment. They also learn to recognize their avoidance mechanisms, determine their index trauma and acquire DBT skills. Trauma-focused therapy is the main focus of phase 2 (weeks 3 - 10). The individual psychotherapy consists primarily of PE, but has elements of cognitive therapy as well. Also, therapists can, after consultation with their client and the treatment team, use EMDR when that seems appropriate. In the third phase (weeks 11-12) the objective is to help clients accept trauma-related elements of their personal history and focus on how they wish to pick-up their daily lives after finishing treatment. Enhancing self-acceptance and self-compassion are integrated throughout the treatment program.

**Table 1 T1:** Overview of modules within clinical DBT-PTSD across the three phases of treatment.

Individual		Group	
Trauma-focused therapy^123^ᵐ Exposure *in vivo* ^23^* Mentor meetings^123^ DBT Diary review^123^ Psychomotor therapy^23^* Systemic therapy^123^*ᵐ	Creative therapy^23^ Nightmare training^23^* Mindfulness^123^ Expert by experience session^123^*ᵐ	Skills training^123^ Psycho-education^12^ Self-worth^23^* Interpersonal effectiveness^23^* Creative therapy^123^*	Psychomotor therapy¹²³ Conquering life³ Mindfulness ¹²³ Sports modules¹²³ᵐ Self-defence^¹²³^

Treatment phase = ¹²³; Optional modules = *; Protocol modifications = ᵐ.

### Measurement instruments

2.6

An overview of all measurements is provided in **Figure 2** and shows which measures are part of ROM at the treatment center. Treatment history is assessed at baseline. At follow-up, we register treatments that clients received after inpatient DBT-PTSD.

**Figure 2 f2:**
[figure not shown]
Overview of enrolment, intervention and assessments (based on the spirit guidelines, 36).

#### Primary outcome: PTSD

2.6.1

The Life Events Checklist-5 (LEC-5) (37, 38) is a self-report measure that assesses type of trauma. It consists of 16 traumatic events that may lead to PTSD. The LEC-5 is administered a as part of regular diagnostics.

With the Clinician Administered PTSD Scale for DSM-5 (CAPS-5) (39, 40) we measure the presence and severity of PTSD. The CAPS-5 has a range of 0-80 with higher scores indicating more severe PTSD symptoms. In the last week of treatment the week-version of the CAPS-5 is standardly used at the treatment Centre to assess PTSD posttreatment (T2). The CAPS-5 has high interrater reliability (ICC = .98) and internal consistency (α = .90) for measuring PTSD severity. Based on considerations expressed by Larsen et al. (41) and Varker et al. (42), we define treatment response as a decrease of ≥9 points (11%) on the CAPS-5, remission as a CAPS-5 score of <12 and sustained PTSD remission at 6 and 12 months follow-up.

We use the PTSD Checklist for DSM-5 (PCL-5) (43) to assess the self-reported severity of PTSD. This questionnaire consists of 20 items with a 5-point Likert Scale (0-4) and has a range of 0-80. It is sensitive to measure change in PTSD symptoms and has good psychometric properties (43, 44).

#### Dissociation

2.6.2

Dissociative experiences are assessed with the Dissociative Experience Scale (DES) (45), a self-report questionnaire that consists of 28 questions (range of 0-100). Items are scored on a Likert-scale varying from 0% (never) till 100% (all the time). Reliability and validity have been confirmed (45, 46).

The Somatoform Dissociation Questionnaire-20 (SDQ-20) (47, 48) is a self-report questionnaire that assesses somatoform dissociative symptoms. Two studies demonstrated convergent and criterion-related validity and high internal consistency in Dutch samples (47). Third, we assess the dissociative subtype (depersonalization and derealization) with two items (range of 0-8) of the CAPS-5.

#### Borderline and parasuicidal behavior

2.6.3

We use the Borderline Personality Disorder Severity Interview (BPDSI) (49) to determine the severity of borderline personality disorder during the past three months. The BPDSI is a 70 item (range 0-90) interview. It has excellent interrater reliability, good internal consistency (α = 0.85) and excellent concurrent and construct validity (49). We use the subscale ‘Parasuicidal’ to assess non-suicidal self-injury and suicidality, because it has good internal consistency (α = .81) (49).

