#### Short and long term effects of DBT-PTSD

3.1.1

To study short-term within-subjects differences, change scores will be calculated with the first three time points (T2-T1=Δtreatment and T1- T0=Δwaiting-list), resulting in four Δ-variables for PTSD, six for dissociation, two for NNSI and suicidal ideation and two for borderline symptomatology. Two-sided paired-samples t-tests will be conducted to compare the Δtreatment and Δwaiting-list scores. We use two-sided tests to maintain a conservative α level. When the anticipated waiting list period turns out to be less than three months, we will consider excluding the participant from the paired t-test analyses. When, at the end of the study, the waiting list period appears to vary much more than expected, and we might need to exclude too many patients, we will consider alternative statistical analyses that are able to deal with this variability, such as linear mixed model analysis. *Post-hoc* analyses to assess long term treatment effects in PTSD, dissociation, NNSI and suicidal ideation, and borderline symptomatology will be carried out with linear mixed model analyses with time as random effects. We will include two predictors of treatment effects on PTSD severity, as measured with the CAPS-5 and PCL-5 into the PTSD model: 1) baseline severity of BPD symptoms (using the total score on the BPDSI) and 2) cluster C personality disorders (with the sum of the dimensional SCID-5-P scores of the three cluster C personality disorders). Further, we will use linear mixed model analyses to study the effects of DBT-PTSD on social functioning and quality of life over time.

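### The posttreatment BPDSI scores describe the 12-week admission, so the two BPDSI tests estimate change during admission and probably attenuate any decrease reached by the end of treatment

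*Protocol article*

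**What the plan says.** Section 2.6.3 uses the BPDSI "to determine the severity of borderline personality disorder during the past three months" and takes its Parasuicidal subscale as the measure of self-injury and suicidality. Section 2.5 gives the length of the admission: "This inpatient, modular DBT-PTSD treatment program of 12 weeks". Section 2.1 places the assessments at the start of the waiting list (T0), then "at pre (T1) and posttreatment (T2) and at six (T3) and twelve months (T4) follow-up", with the wait between T0 and T1 set at about three months.

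For the short-term analysis, section 3.1.1 states that "change scores will be calculated with the first three time points", and T2-T1 is tested against T1-T0 with two-sided paired t-tests. Section 2.8 lists seven such tests. Two of them use the BPDSI: the total score and the Parasuicidal sum score. The hypothesis in the Introduction is that "PTSD, dissociation, parasuicidal behavior and BPD symptoms will decrease significantly after DBT-PTSD", with no significant change over the waiting list.

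For the CAPS-5 the plan adapts the recall period at T2: "In the last week of treatment the week-version of the CAPS-5 is standardly used at the treatment Centre to assess PTSD posttreatment (T2"). No shorter recall period or later T2 is described for the BPDSI.

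**The concern.** A three-month recall period taken at the end of a 12-week admission looks back over the whole admission. The T2 BPDSI score therefore mixes the first weeks, when little may have changed, with the last weeks, when any benefit should be greatest. T1 looks back over the waiting period, and T0 over the three months before that. On this instrument T2-T1 sets the admission against the wait; it does not set the state after treatment against the state before it.

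Two conclusions are at risk. A non-significant BPDSI result could arise from the recall window alone and be read as no effect on borderline symptoms or parasuicidal behaviour. A significant result would be reported as a decrease after treatment, although the score contains little or no time after treatment.

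**Working it through.** **1. The plan's own figure.** Inputs from sections 2.8 and 3.1.1: paired t-test, two-sided alpha 0.01, difference 0.5 SD, power 0.80. With N=51 the noncentrality is 0.5 × √51 = 3.57 on 50 degrees of freedom, and the power is 0.809. N=51 is the smallest size that reaches 0.80, so the stated figure reproduces. Adding 10% gives 51 × 1.10 = 56.1, in line with the stated 56.

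**2. The recall windows.** Put admission (T1) at week 0 and T2 at week 12, and take three months as W = 12 or 13 weeks.

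- T2 covers weeks 0 to 12, or -1 to 12: the admission and at most one week of waiting.
- T1 covers the waiting period.
- T0 covers the three months before the wait.
- T3, six months after treatment, covers roughly months 3 to 6 after discharge and contains no admission time.

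**3. The share of the end change visible at T2.** Three assumptions are mine, not the plan's: the score weights its window evenly, SDs are unchanged, and symptoms are flat before admission. Let f(w) be the fraction of the end-of-treatment change reached by week w. The visible share is k = (1/W) × (area under f from week 0 to week 12).

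- Linear over weeks 0-12: area 12/2 = 6, so k = 6/12 = 0.50 or 6/13 = 0.46.
- Linear over weeks 3-10, then stable: area 8/2 + 2 = 6, so the same k.
- Complete by week 4: area 4/2 + 8 = 10, so k = 0.83 or 0.77.
- Only in weeks 9-12: area 4/2 = 2, so k = 0.17 or 0.15.

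**4. Power at N=51 for a true end-of-treatment effect of 0.5 SD.** With flat symptoms before admission, T0 and T1 are unaffected, and the tested effect is 0.5 × k.

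| Assumed course | k (W = 12 / 13) | Effect seen | Power at N=51 | N for 0.80 |
|---|---|---|---|---|
| Linear (weeks 0-12 or 3-10) | 0.50 / 0.46 | 0.25 / 0.23 | 0.20 / 0.16 | 191 / 223 |
| Complete by week 4 | 0.83 / 0.77 | 0.42 / 0.38 | 0.62 / 0.53 | 71 / 83 |
| Weeks 9-12 only | 0.17 / 0.15 | 0.08 / 0.08 | 0.02 / 0.02 | 1686 / 1978 |

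**5. A larger true effect.** At k = 0.50 a true 1.0 SD effect appears as 0.5 SD and has power 0.81. A true 0.8 SD effect appears as 0.4 SD and has power 0.57.

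**The case against.** The strongest reply is that the tested contrast suits the instrument: two periods of about three months, each measured with a three-month window, and almost no overlap between windows. That is correct, and it is a reason to keep the T2 tests. It supports a statement about change during admission. It does not turn that into a statement about status afterwards.

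The power loss can also be challenged, rightly. Section 2.8 powers for 0.5 SD between the scores as analysed, and for that quantity power at N=51 is 0.81. The lower figures apply only if 0.5 SD is the effect at the end of treatment, and they depend on an assumed course and weighting. They illustrate the problem and do not show an error in the sample size.

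The longer-term data partly cover the gap. Section 3.1.1 plans mixed models for borderline symptoms and self-injury over follow-up, and the diary records self-injury and suicidality daily during admission. But the plan calls those mixed models post hoc, and it does not say that the claim about BPDSI scores after treatment rests on them.

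Four stronger readings are tempting and not supported:

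- *T2 cannot show a decrease.* It can: a fall during admission lowers T2 relative to T1, and a large or early fall may be detected.
- *The first two weeks are untreated.* The text says "Trauma-focused therapy is the main focus of phase 2 (weeks 3 - 10"), but Table 1 marks trauma-focused therapy in all three phases, and DBT skills are taught from phase 1.
- *The ward suppresses self-harm, so the effect is overstated.* The protocol gives nothing on this.
- *The T2 BPDSI is certainly taken in the last week.* That timing is stated for the CAPS-5 only, and the schedule figure is not available here.

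**Conclusion.** The point holds as a mismatch between recall window, time point and hypothesis, all fixed in the protocol itself. The T2 BPDSI total and Parasuicidal scores describe essentially the admission, so two of the seven short-term tests cannot by themselves support a conclusion about the state after treatment. Attenuation of an end-of-treatment decrease is probable; its size is unknown, because the protocol gives neither a symptom course nor a weighting rule for the BPDSI. Under the stated assumptions a true 0.5 SD end effect has power of about 0.16-0.20 with a linear decline, and about 0.02 to 0.62 across the other courses examined.

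These are secondary outcomes. The primary CAPS-5 result is not affected, since its T2 version looks back one week. The point deserves a change because it alters what the trial may conclude about borderline symptoms and parasuicidal behaviour, and the data needed are already collected.

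**What to change.** Keep the two T2 tests, but label and interpret them as change during admission relative to the waiting period, and state that the recall window probably attenuates an end-of-treatment decrease.

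For the BPDSI total and Parasuicidal scores, prespecify the T3 versus T1 contrast in the linear mixed model already planned as the basis for any claim of a decrease after DBT-PTSD. Measurement occasion should enter as a categorical fixed effect so that this contrast is estimated directly. Record the change, with its date, before the researchers receive the data.

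No new assessment is needed. There are three costs, each to be stated with the result. More clients will be lost by T3 than by T2. T1 to T3 spans about nine months (three of admission plus six of follow-up) against a control period of three, so a direct test of T3-T1 against T1-T0 would not compare like with like. Treatment received after discharge, which the study already records, may contribute to the T3 score.
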